### Recruitment

We will recruit a convenience sample of centres within our network of infection control specialists, quality officers and surgeons (western France and Paris area). An introductory email to contacts will be sent by the principal investigator, inviting them and their institution to consider participating. We will then arrange a meeting with surgeons, anaesthetists, managers and chief executives from interested sites to introduce our study and obtain written agreement to participate.

### Assignment of interventions

#### Sequence generation (i.e. randomisation)

Among the 15 centres included in the first study phase, 7 centres (clusters) will be randomly allocated to the intervention arm. During the second phase, 8 centres among the 15 remaining will be randomly allocated to the intervention arm (Additional file 1). A statistician, blinded to cluster identity and not involved in delivering the intervention, will generate the allocation sequence using computer-generated random numbers. The allocation sequence will be generated, including the hospital type (university hospitals, general hospitals and private hospitals) as a factor for stratification. This stratification is motivated by differences in organisation, staffing and patient recruitment across these hospital categories.

**Fig. 3 Fig3:**
[figure not shown]
Description of data collected, data sources and key variables for the merging according to levels. OR, operating room; eCRF, electronic case report form; ICD-10*, International Statistical Classification of Diseases and Related Health Problems, 10th Revision*; POC, post-operative complication

#### Blinding

Surgical staff will be aware of the intervention they provide during the intervention period (i.e. they are not blinded). The statistician performing the analysis will be blinded to the identification of the sites. In both the intervention and the control conditions, the patients will be informed through a letter that the site is participating in a research study. Medical doctors specialising in the analysis of data from the local and national hospital discharge database of diagnosis and procedure codes will be blinded to the randomisation arm.

### Data collection and management

Information will be collected at three different levels. At the centre level, we will collect data on randomised hospitals (status and surgical activity) and their surgical environment characteristics (air changes of filtered air per hour, positive pressure, temperature, relative humidity, particle contamination class, kinetics of particle decontamination class). Characteristics of senior surgeons performing hip/knee replacements will be recorded (age, gender, function, experience in the function, role in the surgical procedure). At the patient level, variables on intra-operative staff behaviour (frequency of door opening and noise levels), the patients and surgical procedures (patient ID number, type of procedure, date, incision time, wound closure time and the OR ID) will be collected. These data will be collected by the network of wireless sensors described above and by extraction from OR information systems.

A list of each patient’s comorbidities and crude post-operative events will be extracted from the local and the national hospital discharge database (PMSI) and the ICD-10 (Table 1 and Fig. 3). The primary outcome of the study, as defined above, will be identified using algorithms previously developed for the PMSI and ICD-10 databases to assess patients’ outcomes after hip replacement [6, 38]. A complementary assessment will be performed using specific algorithms for SSI [39]. This algorithm previously developed for detecting hip or knee arthroplasty-related infections, showed a sensitivity (Se) of 98% (97.1–98.9) and a specificity (Spe) of 71 (67.8–73.4), a positive predictive value (PPV) of 63% (59.8–65.8) and negative predictive value (NPV) of 99% (98.1–99.5). Using a more specific case definition, based on a sample of 681 hospital stays, Se was 97%, Spe was 95%, PPV was 87%, and NPV was 98% [39].

### Statistical methods

#### Data analysis

The results from the statistical analyses will be reported according to the Consolidated Standards of Reporting Trials (CONSORT) statement recommendations and its extensions for cluster randomised trials and for non-pharmacological interventions. No interim analysis will be performed. All eligible patients will be taken into account according to the initial allocation. OR, surgeon and patient characteristics will be reported using descriptive statistics. The primary outcome will be analysed using a logistic mixed model taking into account the stratification factor as a fixed effect [40]. Patients will be the unit of analysis and will be considered embedded with surgeons who will themselves be considered embedded in orthopaedic centres. Adjusted analyses may also be performed, notably in the case of baseline imbalance, a situation often encountered in cluster randomised trials, notably due to a limited number of randomisation units. A sensitivity analysis may also be planned depending on the results observed as regard to the adherence to the intervention. Intraclass correlation will be estimated within each group.

For secondary outcomes, components of the primary outcome will be analysed with an equivalent method as for the main criteria. The frequency of doors opening will be analysed with a mixed effect Poisson regression model with the duration of procedure as offset. The duration of hospital stay and the surgical intervention duration (from wound incision to closure) will be analysed using a mixed linear model after application of a Box-Cox transformation if necessary.

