### Study timeline

The study will start with a baseline period of 3 months during which data on door opening and noise levels will be collected in the 30 ORs included (Fig. 2). The intervention period will last 6 months per centre. The centres will be included in two successive phases: a first phase including 15 centres (7 in the intervention arm and 8 in the control arm) and the 15 remaining centres in a second phase (8 in the intervention arm and 7 in the control arm). These two phases will be separated by a baseline period of 3 months (Fig. 2). This choice has been made for logistic reasons, to ease the installation of monitoring systems and the implementation of the intervention in a smaller group of centres. A post-intervention period of 6 months, keeping the monitoring system in place in the 30 ORs, will be used to assess the sustainability of the intervention. Due to the delay in the coding process of hospital discharge data and ICD-10 codes, we will analyse the outcomes at the end of our trial only.

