### Sample size

This multicentre interventional study will include 30 healthcare facilities (HCFs) that represent 65 ORs for orthopaedic surgery. We made the hypothesis of a difference of POC rates of 7% vs 10%. Considering power of 80% (alpha = 5% bilaterally), we would need to include 2706 patients if the randomisation was individual. Because this trial is cluster randomised, an inflation factor has to be applied to this sample size, taking into account the correlation between patients clustered within a common cluster. In our design, patients are embedded with surgeons who are embedded in orthopaedic centres, which are randomly allocated. For the sample size calculation, we considered clustering at the surgeon level only, based on the assumption that the inter-patient correlation is stronger at the surgeon level than at the hospital level. Thus, considering the surgeon as the unit of clustering with an intraclass correlation coefficient of 0.05 and an average number of 54.5 patients per surgeon for a 6-month period, we calculated that 183 surgeons will be required, for an overall population of 9945 patients. Therefore, randomising 30 centres each accounting for an average of 6 surgeons allows the inclusion of 9945 patients to provide the nominal power to our trial. Although only the surgeon level correlation was taken into account in the sample size calculation, the statistical analysis will take into account the more complex hierarchical structure of the design.

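### Centres are randomised separately in two inclusion phases (7:8, then 8:7), but the primary model, as written, adjusts for hospital type and not for phase

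*Protocol article*

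**What the plan says.** Under Sequence generation, the protocol article fixes two draws. For the first: "Among the 15 centres included in the first study phase, 7 centres (clusters) will be randomly allocated to the intervention arm". For the second: "During the second phase, 8 centres among the 15 remaining will be randomly allocated to the intervention arm". The Study timeline section repeats the counts, describes the phases as successive and adopted for logistic reasons, and says "These two phases will be separated by a baseline period of 3 months".

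The same Sequence generation section says the sequence is generated "including the hospital type (university hospitals, general hospitals and private hospitals) as a factor for stratification". Phase is not called a stratification factor anywhere.

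Under Data analysis, the primary outcome is analysed with a "logistic mixed model taking into account the stratification factor as a fixed effect", with patients nested in surgeons and surgeons in centres. Components of the composite get an equivalent method. Door opening has its own mixed Poisson model with procedure duration as offset and no covariates listed. No model is given for noise. Further adjustment is optional: "Adjusted analyses may also be performed, notably in the case of baseline imbalance".

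**The concern.** Fixing the number of intervention centres within each phase restricts the randomisation by phase, whether or not phase is labelled a stratum. The usual rule is to analyse by the factors used to randomise. Here the model refers to one factor in the singular, and the only factor named is hospital type.

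The phases differ in calendar time and in order of installation, and the outcome comes from routine hospital discharge coding. A difference in recorded complication rates between phases is therefore possible, though the article gives no evidence of one. If it exists, two things follow. The difference sits in the unexplained between-centre variance, so the standard error is larger than the design warrants. And because the ratio changes from 7:8 to 8:7, arm is weakly associated with phase, so a small part of the difference enters the treatment effect. With only 30 randomised units, avoidable centre-level noise is worth removing.

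**Working it through.** **Inputs from the Sample size section:** rates 7% and 10% (mean 8.5%, target difference 3 points), 80% power, two-sided 5%, 2706 patients if individually randomised, intraclass correlation 0.05, 54.5 patients per surgeon, 9945 patients in 30 centres. **Assumed, because the article gives no figure:** a phase difference d of 1, 2 or 3 points.

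**The plan's own figure.** A two-proportion calculation (pooled variance, no continuity correction) gives 1356 per arm, 2712 in total, close to the stated 2706. The design effect is 1 + (54.5 − 1) × 0.05 = 3.675. Then 2706 × 3.675 = 9944.55, or 9945, and 9945 / 54.5 = 182.5, or 183 surgeons. The stated size reproduces and does not depend on this point.

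**Association of arm with phase.** The probability of intervention is 7/15 = 46.7% in phase 1 and 8/15 = 53.3% in phase 2. The correlation is (8 × 8 − 7 × 7) / 225 = 0.067.

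**Bias.** With phase omitted, the risk difference is shifted by d × (8/15 − 7/15) = d/15.

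**Variance.** Patients per centre: 9945 / 30 = 331.5. The planning variance of a centre proportion is 0.085 × 0.915 × 3.675 / 331.5 = 0.000862. Two equal phases differing by d add (d/2)² to the apparent variance.

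**Power and type I error.** At 80% power the target effect is 1.960 + 0.842 = 2.802 standard errors. The number of centres per arm is fixed within each phase, so omitting phase does not widen the true sampling distribution of the estimate. It inflates the estimated standard error by a factor s, the square root of 1 plus the added share, and shifts the estimate by b = (d/15)/0.03 of the target. Power is then Φ(2.802 × (1 ∓ b) − 1.96 × s). The minus sign applies when phase 2 has the higher complication rate (the shift hides benefit) and the plus sign when it has the lower. Type I error is Φ(−1.96s + 2.802b) + Φ(−1.96s − 2.802b).

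| d (points) | Bias (points) | Share of 3 points | Added variance | s | Power, phase 2 higher | Power, phase 2 lower | Type I error |
|---|---|---|---|---|---|---|---|
| 0 | 0 | 0% | 0% | 1 | 80% | 80% | 5.0% |
| 1 | 0.07 | 2% | 2.9% | 1.014 | 77.4% | 80.9% | 4.7% |
| 2 | 0.13 | 4% | 11.6% | 1.056 | 72.8% | 80.4% | 4.0% |
| 3 | 0.20 | 7% | 26.1% | 1.123 | 66.1% | 78.5% | 3.0% |

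A cruder version treats the added variance as real and ignores the bias. It gives Φ(2.802/1.056 − 1.96) = 75.6% at 2 points, between the two directions. As odds ratios, the biases are factors of about 1.009, 1.017 and 1.026.

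**Simulation check.** Set-up: 30 centres, 6 surgeons per centre, 55 patients per surgeon, surgeon-level correlation 0.05, no extra centre variance, and a linear model on centre proportions.

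- With no phase difference, power is 75% with or without phase.
- With phase 2 higher by 2 points, power is 68% without phase and 76% with it. At 3 points it is 63% and 77%.
- With phase 2 lower by 2 points, power is about 77% either way.
- Type I error without phase is 4.4% at 2 points and 3.2% at 3 points. With phase it stays between 4.2% and 5.5%.

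This is a centre-level approximation. It is not the planned mixed model and does not include hospital type.

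**The case against.** The best defence is that this is a condensed article. It says hospital type is included as a stratification factor, not that it is the only one, and a full list of fixed effects could stand in the complete protocol or analysis plan. That carries some weight, but the article does state the fixed effect in the singular and names one factor, so a reader following it would omit phase. The optional adjusted analyses do not close the gap: they are not primary, they depend on observed imbalance, and they name no covariate.

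The second defence is size. The totals balance at 15:15, the bias is small, and the phase differences are assumed. Two points is about a quarter of the mean rate and 3 points equals the whole target effect, for phases separated by a 3-month period. At 1 point the effect on power is slight, and in one direction there is no loss even at 2 points. All of this stands and limits the point to a modest one.

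A reader might infer more than the article supports:

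- **A false-positive risk.** The mismatch in the standard error runs the other way, and type I error falls below 5%.
- **A wrong adjustment set for every secondary outcome.** The equivalent method covers only the components of the composite. The door-opening model lists no covariates and noise has no stated model, so no wrong covariate set is shown for either.

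**Conclusion.** The point holds in a limited form. Phase restricts the randomisation, and the primary model and the component models as described leave it out. The omission does not threaten validity in the sense of false positives, and the stated sample size is unaffected. Its cost is a conservative test, a possible loss of power, and a bias of d/15 in either direction. Over the assumed 1 to 3 points the power cost runs from nil to about 14 percentage points. The top of that range needs a 3-point difference with the higher rate in phase 2. Every magnitude rests on an assumed phase difference, and at zero difference nothing is lost. The case for the change is that the analysis should follow the design and that doing so is almost free. The trial's conclusion has not been shown to depend on it.

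**What to change.** Under Sequence generation, state that allocation is stratified by inclusion phase and hospital type. Under Data analysis, name hospital type and inclusion phase (two levels) as fixed effects in the primary model and in the models for the components of the composite. Add phase to the door-opening model as well, since its covariates are not stated.

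The cost is a phrase in each section and one degree of freedom: 30 centres less intercept, arm and two hospital-type terms leaves 26, and adding phase leaves 25. No change to sample size, allocation or data collection is needed. Fixing this before the outcome data are analysed also avoids a later choice about whether to adjust for phase.

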#### Patient eligibility criteria

The population will comprise patients ages 18 years or older undergoing the surgical procedure of knee or hip arthroplasty (replacement or resurfacing) as a primary, elective or urgent referral. Patients undergoing arthroplasty revision and patients with previous SSI will not be eligible. All surgical procedures will be included, whatever the age, gender, experience and position of the patient’s senior orthopaedic surgeon.

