### Outcomes

The primary outcome is the occurrence of any major POC (i.e. a composite of SSI, thromboembolic complications, unplanned surgical revision, in-hospital mortality, myocardial infarction, cardiac failure, stroke, renal failure/dialysis and sepsis) (Table 2) during the postoperative period, up to 30 days after the procedure (90 days for SSI). We will also evaluate readmission for any cause within 72 h after initial hospital discharge, ICU admission and in-hospital mortality during readmission. Secondary outcomes will include each of the individual components of the composite described above [37]. The registry-based design uses routinely collected data to ascertain our outcomes. In France, we have databases of routinely collected data on hospital discharge (acronym PMSI, hospital billing records) and *International Statistical Classification of Diseases and Related Health Problems, 10th Revision* (ICD-10) details. Algorithms previously built for the analysis of these databases will be used to assess the patient outcomes [6, 38]. A complementary analysis will be performed using specific algorithms for SSI [39]. Specialists in charge of this analysis will be blinded to the randomisation arm. Secondary outcomes are the occurrence of POC including whole individual items of the composite criterion, the occurrence of SSI or any wound complication (superficial, deep, organ/space, or a problem of healing) up to 90 days following the procedure, the number of door openings, and the level of noise automatically collected by a network of sensors placed in the OR.

**Table 2 Tab2:** Patient comorbidities and post-operative complications obtained from the French National Hospital Discharge Database and the *International Statistical Classification of Diseases and Related Health Problems, 10th Revision* (ICD-10)

Patient characteristics/comorbidities	Post-operative complication
Age	Surgical site infection
Gender	Thromboembolic complications
Public/private centre	Unplanned surgical revision
Elective/emergency	In-hospital mortality
Hypertension	Myocardial infarction
Ischemic heart disease	Cardiac failure
Cardiac arrhythmia	Stroke
Chronic heart failure	Renal failure/dialysis
Heart valve disease	Sepsis
Peripheral vascular disease	ICU admission
Dementia	Readmission within 72 h of discharge
Cerebrovascular disease	In-hospital mortality during readmission
Hemiplegia or paraplegia	
Chronic obstructive pulmonary disease	
Pulmonary circulation disorder	

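### Case-mix adjustment of the primary outcome is optional and prompted by observed imbalance; fixing it in advance would gain precision from data already collected

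*Protocol article*

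**What the plan says.** Protocol article, Data analysis: "The primary outcome will be analysed using a logistic mixed model taking into account the stratification factor as a fixed effect". Patients are nested in surgeons and surgeons in centres. The stratification factor is set under Sequence generation, where the allocation sequence is described as "including the hospital type (university hospitals, general hospitals and private hospitals) as a factor for stratification". No other covariate is named for the primary model.

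On further adjustment the section says: "Adjusted analyses may also be performed, notably in the case of baseline imbalance". It describes such imbalance as "a situation often encountered in cluster randomised trials, notably due to a limited number of randomisation units". A separate sentence concerns adherence: "A sensitivity analysis may also be planned depending on the results observed as regard to the adherence to the intervention".

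Patient eligibility criteria admits adults "undergoing the surgical procedure of knee or hip arthroplasty (replacement or resurfacing) as a primary, elective or urgent referral". Table 2 under Outcomes, titled "Patient comorbidities and post-operative complications obtained from the French National Hospital Discharge Database", lists age, gender and "Elective/emergency" among the patient characteristics. Data collection and management adds the type of procedure.

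**The concern.** Thirty centres are randomised, 15 per arm, so patient case mix can differ between arms by chance more than it would with individual allocation. The plan foresees this. Its answer is an optional analysis, prompted mainly by looking at the data, with nothing on how the adjusted result is to be read beside the primary one.

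Two things are at stake. The first is precision: if urgency or joint predicts complications and its share varies between centres, leaving it out of the model adds between-centre noise to the treatment comparison. The second is interpretation: if the adjusted and primary estimates disagree, the plan does not say what weight the adjusted one carries.

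The covariate list could sit in an analysis plan that is not shown, so its absence is not the point. The point is the rule the article does state. Adjustment fixed in advance would be better than adjustment prompted by imbalance.

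**Working it through.** **1. The plan's own sample size.** Inputs from Sample size: 10% vs 7%, two-sided alpha 5%, power 80%, ICC 0.05, 54.5 patients per surgeon.
- Per arm, unpooled variance: (1.960 + 0.842)² × (0.10×0.90 + 0.07×0.93) / 0.03² = 1352.6, so 1353 per arm and 2706 in total, as stated.
- Design effect: 1 + (54.5 − 1) × 0.05 = 3.675.
- 2706 × 3.675 = 9944.6, so 9945 patients; 9944.6 / 54.5 = 182.5, so 183 surgeons.

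These figures reproduce and are not in dispute. The calculation takes no credit for covariates.

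**2. How large chance imbalance could be.** Assumed, not in the document: complication risk 25% in urgent and 7% in elective cases. An overall 10% then implies an urgent share of (0.10 − 0.07)/(0.25 − 0.07) = 17%. With a between-centre SD *s* of the urgent share, the standard error of the arm difference in share is *s* × √(1/15 + 1/15). A one-standard-error imbalance moves the unadjusted risk difference by that amount × 0.18.

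| Assumed *s* (points) | SE of arm difference (points) | Shift in risk difference (points) | Share of the 3-point target |
|---|---|---|---|
| 6 | 2.2 | 0.4 | 13% |
| 12 | 4.4 | 0.8 | 26% |
| 15 | 5.5 | 1.0 | 33% |

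This is chance variation, not bias. It also ignores stratification by hospital type, which would remove any part of the spread that lies between hospital types.

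**3. What adjustment would recover.** Illustrative simulation: 30 centres × 6 surgeons × 55 patients, mean urgent share 20%, centre SD 0.30 and surgeon SD 0.20 on the logit scale. The treatment odds ratio is (0.07/0.93)/(0.10/0.90) = 0.68. Analysis is by centre-level t-test, either on raw rates or on rates after subtracting the events expected from urgency. There were 3,000 trials per scenario under the effect and 4,000 under the null.

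| Odds ratio for urgency | Centre SD of urgent share (points) | Power unadjusted | Power adjusted | Gain (points) |
|---|---|---|---|---|
| 2 | about 12 | 0.748 | 0.781 | 3.3 |
| 3 | about 12 | 0.698 | 0.773 | 7.5 |
| 3 | about 6 | 0.766 | 0.784 | 1.8 |
| 5 | about 12 | 0.607 | 0.787 | 18.0 |

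Limits: these are not fits of the planned logistic mixed model, allocation was not stratified, and only urgency was adjusted for. The elective risk was held near 7.5%, so the overall control rate was not exactly 10% in every row.

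**4. Type I error in the same scenarios.**
- Unadjusted model fixed in advance: 0.046 to 0.056.
- Adjusted model fixed in advance: 0.050 to 0.054.
- Adjusting only when the arms differ by more than 5 points in urgent share: 0.030 to 0.054.
- Reporting the smaller of the two p-values: 0.068 to 0.079.

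The imbalance trigger does not inflate error. Only free choice between the two results does, and the plan does not provide for that.

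**The case against.** The strongest reply is that nothing is broken. The primary model is named, it includes the factor used to stratify, and the word *also* makes adjusted analyses additional. Stratification was chosen partly because patient recruitment differs across hospital types, so some case mix is already handled. A model with centre as a level carries the remaining between-centre variation in its standard error. Nowhere does the document call urgency a strong predictor; Table 2 only lists it. With a narrow spread between centres the gain is under 2 points of power. An analysis without patient covariates, supplemented by adjusted ones, is a legitimate design.

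All of that stands, and it rules out several stronger readings:
- A reader might infer that the primary effect can be chosen after seeing the data. It cannot; only the existence and weight of a supplementary estimate are open.
- A reader might infer that adjustment prompted by imbalance inflates type I error. Step 4 does not show this.
- A reader might take the shifts in step 2 as bias. They are random variation under assumed figures.
- A reader might take the adherence sentence to mean an analysis chosen on outcome results. It refers to observed adherence, and Study timeline says outcomes are analysed only at the end of the trial.

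The reply does not explain why a foreseen problem should be met with an optional analysis when the main case-mix variables are in hand and could be fixed beforehand.

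**Conclusion.** The point holds as an inexpensive improvement in efficiency and clarity, not as a flaw in validity. The stated primary analysis is unbiased and keeps its error rate. Leaving case mix out of it gives up precision: roughly 2 to 18 points of power in the scenarios tried. The low end applies when urgency varies little between centres, the high end when it is a strong predictor and varies widely. Those inputs are assumptions, and stratification by hospital type may reduce the gain. Whether an adjusted estimate is produced, and how it is weighed against the primary one, is left unsettled.

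**What to change.** Replace the sentence on adjusted analyses with wording such as: *The primary logistic mixed model adjusts, whatever the observed balance, for hospital type, joint (hip or knee), elective/emergency, age and gender. The model adjusted for hospital type alone is a sensitivity analysis. A standardised risk difference is reported alongside the odds ratio.*

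Keep the Table 2 comorbidities for a supplementary model unless they can be shown to predate surgery. Comorbidities and complications come from the same discharge records, and several pairs lie close together (chronic heart failure and cardiac failure, chronic renal failure and renal failure/dialysis). Coding may therefore mix a baseline condition with an outcome, and adjusting for it could remove part of the effect.

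The cost is a change of wording and a slightly longer model, with no new data. It can be made before outcomes are examined. One small downside is that the conditional odds ratio will differ slightly from the less adjusted one. The standardised risk difference deals with this, and it matches the scale of the 7% vs 10% hypothesis.
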